### Statistical analysis

#### Descriptive statistics

Mean, median and standard deviations or median and ranges, if appropriate in case of skewed distributions, of descriptive parameters of primary and secondary outcomes will be reported.

#### Univariate analysis

Univariate analysis will be carried out using χ^2^-tests for dichotomised outcomes and T-tests for continuous outcomes. Intention-to-treat analysis will be used for cases that crossed over to other interventions.

•Primary analysis

The χ^2^-test will be used to test for differences between groups on union and stability at 52 weeks (α = 0.0167). T-test will be used to test for differences between groups on NDI improvement at 52 weeks (α = 0.0167).

•Secondary analysis

The χ^2^-test will be used to analyse the difference in dichotomised NDI. NDI will be dichotomised using the criterium of the minimal clinically important change (improvement) of 7.5 points out of 50. The relation between radiological parameters (union and stability) and NDI will be analysed by comparing the average NDI improvement for patients that acquired union/stability with those that did not.

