**Methods/Design:**

The trial is an observational study in which eleven centres in five European countries are involved. All patients admitted to one of these centres who meet the selection criteria (≥55 years, acute (<two weeks) type II/III odontoid fracture, no rheumatoid arthritis, no ankylosing spondylitis, no previous treatment for odontoid fracture) are asked to participate. The applied treatment is in accordance with usual care and chosen by the treating surgeon and patient. A cohort of 275 patients will be included. Clinical and radiological follow-up moments are scheduled at 6, 12, 26, 52 and 104 weeks, at which both surgeon and patient will complete Case Record Forms (CRFs). The primary outcome will be a combination of fracture healing and clinical outcome at 52 weeks. Osseous union and fracture stability will be assessed with CT-imaging and dynamic X-ray. Clinical outcome will be scored by the Neck Disability Index (NDI) and correlated to the imaging data. Additionally, predefined subgroup analysis will be carried out (i.e. for patient age and osteoporosis) and prognostic factors will be identified.

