## Background

In the elderly, odontoid fractures are the most common fractures of the cervical spine [1-6]. As the population ages, their incidence and relevance to clinical practice are expected to increase [7]. The treatment for patients with fractures of the odontoid process is based on the fracture pattern, the patient’s medical condition [2] including age, pain, neurological deficits, and the surgeon’s personal preference. Surgical treatment involves anterior odontoid screw fixation or posterior (cranio)atlanto-axial arthrodesis, leading to prompt stability of the upper cervical spine. However, the condition of the patient may deteriorate by undergoing (major) cervical spine surgery [8]. Especially in the very old (≥80 years of age), a surgical intervention has significant risks for the patient. An alternative to avoid the possible complications of cervical spine surgery is conservative treatment with rigid or non-rigid immobilisation for a longer period of time. However, such immobilisation may eventually result in non-union and prolonged fracture instability, requiring secondary surgery [9]. This unnecessarily lengthens treatment duration and, worse, can cause significant deterioration of the cervical spine anatomy and the patient’s condition [10].

Finding the right balance between fracture healing and treatment complications is difficult. In very old patients, finding this balance is even more challenging. In hospitals where upper cervical spine surgery is frequently performed, it is becoming increasingly common to operate on even the very old patient with a cervical spine fracture. However, debate remains as to whether or not this is indeed a favourable development.

Currently available literature reviews on this topic were inconclusive [11,12]. Recent clinical studies focussed on survival and the occurrence of complications, but not on fracture union and stability [13,14]. All other performed clinical studies were carried out retrospectively, were of limited quality and most did not specifically focus on elderly patients. Moreover, minimal attention was paid to grounds for chosen treatments, and patient groups were often poorly comparable. In the vast majority of published studies, only a small number of patients were included (typically <50).

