Furthermore, the goal of treatment is still debatable. It is unknown whether or not non-union always leads to complaints in the patient. Consequently, debate remains as to whether the goal of treatment should be osseous union, fracture stability or a favourable clinical outcome. The measurement of these parameters is likewise not uniformly described. The available literature shows higher osseous union rates in surgically compared to conservatively treated patients (66–85% and 28–44%, respectively), but patient selection mechanisms may have profoundly interfered with these outcome percentages. The majority of patients achieved fracture stability regardless of the applied treatment (82-97% in surgically treated patients and 53-79% in conservatively treated patients). There are insufficient data available, especially from direct comparisons, to determine the difference in clinical outcome between surgical and conservative treatment strategies. There is no evidence that clinical outcome correlates better to fracture union than to fracture stability, or that the quality of union, whether it be osseous of fibrous, influences clinical outcome [12].

The goal of this study is to prospectively compare fracture union, fracture stability and NDI improvement at 52 weeks between surgical and conservative treatments in patients over 55 years of age with acute type II and III odontoid fractures. Predefined subgroup analysis may offer prognostic factors that can predict the success of either a surgical or conservative treatment. The influence of age (≥55-80 and ≥80 years) on treatment outcome will particularly be studied. The outcome of this study will yield valuable information enabling more rational decision making in treating the elderly patient population.

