### Treatment

The treating surgeon and patient will make a shared decision as to whether surgical or conservative treatment will be applied. Participating centres and surgeons are all able to facilitate and respectively carry out both surgical and conservative treatments.

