#### Multivariate analysis

Multivariate analyses will be carried out using regression models with dichotomised union, stability and NDI as dependent variables, and with the secondary outcome parameters as independent variables and covariates. Propensity score analysis will be used to generate a model to predict the treatment received with the baseline variables:

•Patient age (both dichotomised (≤80 and >80 years) and continuous)

•Fracture characteristics (type of fracture)

•Fracture displacement (in mm and direction)

•Severity of osteoporosis in C2

•Facet joint degeneration in C1-C2

•NDI

•MDI

•VAS neck pain

•SF-36

•EQ-5D

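### The only analysis labelled primary is an unadjusted comparison of groups formed by surgeon and patient choice, so the primary answer is open to confounding by indication

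*Protocol article*

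**What the plan says.** - **Allocation.** The Treatment section states: "The treating surgeon and patient will make a shared decision as to whether surgical or conservative treatment will be applied". The abstract calls the study observational and says: "The applied treatment is in accordance with usual care and chosen by the treating surgeon and patient".
- **What drives the choice.** The Background says: "The treatment for patients with fractures of the odontoid process is based on the fracture pattern". It adds the patient's medical condition (with age, pain and neurological deficits) and the surgeon's preference.
- **Earlier studies.** Of published union rates after surgery and conservative care, the Background warns that "patient selection mechanisms may have profoundly interfered with these outcome percentages".
- **Primary analysis.** Under Univariate analysis, the item labelled primary is a χ²-test that "will be used to test for differences between groups on union and stability at 52 weeks" and a t-test on NDI improvement at 52 weeks, all at α = 0.0167. No covariate enters.
- **Sample size.** The 0.05 is divided by three for these three hypotheses. The article derives 275 (union), 198 (stability) and 93 (NDI), and takes 275.
- **Adjusted work.** The Multivariate analysis section plans regressions of dichotomised union, stability and NDI, with the secondary outcome parameters as independent variables and covariates. It then says: "Propensity score analysis will be used to generate a model to predict the treatment received with the baseline variables", and lists those variables.
- **Subgroups.** Age and osteoporosis subgroups are predefined. The Discussion intends to evaluate patients below and above 80 years separately.

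**The concern.** The Discussion's aim is comparative: to find the more favourable strategy. Several stated drivers of treatment choice, such as age, fracture pattern and medical condition, plausibly also affect union, stability and NDI. A crude test between such groups mixes any treatment effect with differences in who was treated. Dividing α by three controls multiplicity and does nothing about this mixing.

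At stake is whether the headline result answers the trial's question. Followed as written, the plan exposes its own primary result to the selection problem it identifies in the literature. If an adjusted analysis were promoted only after the data were seen, it would look post hoc.

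**Working it through.** **1. What the sample size was built for.**

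Inputs from the Sample size section: two-sided α = 0.05/3 (z = 2.394), 80% power (z = 0.842), ratio 2:1, dropout 10%.

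- *NDI* (difference 7.5, SD 10): conservative n = (1 + 1/2) × [10 × (2.394 + 0.842)/7.5]² = 27.9, so 28. Adding 56 surgical gives 84, and 84 × 1.1 = 92.4, so 93, the stated figure. (84/0.9 would give 94.)
- *Union*: the base rates behind the 20-point difference are not stated, so 275 cannot be checked uniquely. The pooled two-proportion formula at an assumed 58% v 78% gives 82 + 164 = 246, and 246/0.9 = 273.3, so 274, which is close to 275.

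The NDI figure is exactly that of an unadjusted two-group test, and the union figure is consistent with one. No allowance for adjustment is visible.

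**2. Size of the problem for union (illustration).**

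Analysed patients: 275 × 0.9 ≈ 247, split 2:1 into 165 surgical and 82 conservative. Assume no true treatment effect and a binary prognostic factor present in 30% of surgical and 60% of conservative patients. The factor lowers union by *d* from a base rate of 50% to 80%. The documents give none of these confounder values.

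Spurious difference = (0.60 − 0.30) × *d*.

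One case in full (base 60%, *d* = 30 points):
- surgical 0.60 − 0.30 × 0.30 = 0.51; conservative 0.60 − 0.60 × 0.30 = 0.42; difference 0.09
- pooled rate 0.480, null standard error 0.0675, alternative standard error 0.0670
- P(reject) = Φ[(0.09 − 2.394 × 0.0675)/0.0670] = Φ(−1.07) ≈ 0.14

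Over base rates of 50-80%, by this formula and by simulation:

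| Effect of factor on union | Spurious difference | Rejection at 0.0167 |
|---|---|---|
| 20 points | 6 points | about 6-9% |
| 30 points | 9 points | about 14-17% |
| 40 points | 12 points | about 27-30% |

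The nominal rate is 1.67%.

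**3. The same for NDI.**

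With SD 10, the standard error is 10 × √(1/82 + 1/165) = 1.35. An assumed bias of 2, 3 or 4 points gives rejection in about 18%, 43% or 71% of studies.

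**4. Does the planned adjusted work supply the primary answer?**

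- The propensity score's stated use is to predict the treatment received. Its link to the outcomes is not stated.
- The regressions do not name treatment group as a term. Their covariates are the secondary outcome parameters, which in the Secondary outcome section include complications and secondary surgery. These occur after treatment starts, so conditioning on them can remove part of the effect or add bias.
- No α or sample size is attached to any adjusted contrast.

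**5. Cost of adjusting.**

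Approximate the variance inflation as 1/(1 − R²), with R² the share of treatment choice explained by the covariates (assumed; any gain from prognostic covariates is ignored).

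| R² | Power, 58% v 78% | Power, 60% v 80% | N to offset (275/(1 − R²)) |
|---|---|---|---|
| 0 | 80% | 82% | 275 |
| 0.1 | 76% | 77% | 306 |
| 0.2 | 70% | 72% | 344 |
| 0.3 | 63% | 65% | 393 |

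Stability and NDI need only 198 and 93 by the article's own figures, so the cost falls mainly on union.

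**The case against.** The strongest reply is that the article already plans adjustment: a propensity score on a list of baseline variables, placed directly after regressions on the three outcomes. A condensed article may leave the technique (matching, weighting or covariate) to a fuller document. This stands as far as it goes. A reader might infer that the score is never applied to the outcomes, but the text is silent on this and does not say so. The label remains, however: the article itself fixes the crude tests as primary.

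The primary and secondary items are also bullets under the univariate heading, so they might be read as a first step before the multivariate one. The α of 0.0167 attached to them, matching the Sample size section, counts against that reading.

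The age and osteoporosis subgroups would help expose an artefact due to those factors. They are not the primary comparison and cover only some of the stated drivers of choice. Intention-to-treat, in the Data analysis section, deals with cross-over after treatment is chosen and not with baseline imbalance. Using NDI improvement addresses baseline NDI level at most.

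Finally, the illustration's inputs are assumed and all point towards surgery. That is correct: they show scale, not a prediction.

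**Conclusion.** The point holds as a badly chosen stated rule, and it should be corrected before analysis. The only analysis labelled primary is unadjusted, in a cohort where treatment is chosen partly on plausible prognostic grounds.

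The size is conditional. Under the assumed 30% v 60% imbalance, the chance of a false positive on union rises from 1.67% to between about 6% and 30%. With a smaller imbalance or a weaker factor it would be lower.

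A reader might go further and infer that the result *is* confounded, or is biased in favour of surgery. The documents do not support this. They give no distribution of prognostic factors by treatment, so neither size nor direction is known, and selection could also work against surgery.

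**What to change.** Name a propensity-adjusted treatment effect (weighted or covariate-adjusted) as the primary analysis for union, stability and NDI improvement, at α = 0.0167 each. Build the score only from the baseline variables listed under Multivariate analysis, and keep post-treatment variables such as complications and secondary surgery out of the treatment contrast. Report the χ²-test and t-test as unadjusted, descriptive results.

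The listed variables are already planned, so the wording and analysis work are modest. Two costs should be stated:
- **Precision.** At R² of 0.1-0.3 and union rates near 58-60% v 78-80%, power for union falls from about 80-82% to between about 77% and 63%. Restate the power of 275 for the adjusted analysis.
- **Residual confounding.** General medical condition, neurological deficits and surgeon preference are named as drivers of choice but are not explicit items in the list. Whether the baseline general status item in Table 3 covers the first two is not stated. Confounding by these factors may remain and should be acknowledged.

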### Patient selection

All patients admitted to one of the participating centres who meet the selection criteria will be asked to participate in the study (Table 2). Prior to the start of treatment, the patient will be enrolled by notification to the SIPS Group. The inclusion of patients will continue until the target sample size is reached.

**Table 2 T2:** Selection criteria

**Inclusion criteria**	• At least 55 years old
	• Acute type II and III odontoid fracture based on the classification by Anderson and d’Alonzo (possibly in combination with other fractures); diagnosed using computed tomography
	• Less than two weeks post injury
	• Informed consent
**Exclusion criteria**	• Rheumatoid arthritis
	• Ankylosing spondylitis
	• Previous treatment for odontoid fracture
	• Communication with patient is hampered (e.g. language barrier, severe cognitive impairment, coma)

During baseline and follow-up appointments, radiological and clinical data will be gathered. Patients will also be sent questionnaires to answer at home. Questionnaires will focus on pain intensity, general wellbeing, perceived recovery and illness-related inconveniences.

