### Baseline assessment

After inclusion and prior to the start of treatment, both surgeon and patient will complete the first set of CRFs. In the case of a surgical treatment, the surgeon will complete a CRF directly after surgery and the patient will complete a second set of CRFs three days after surgery to assess the short-term effect of the operation for the patient. In the case of a conservative treatment, the surgeon will complete a CRF after the application of the immobilisation device.

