### Primary outcome

The primary outcomes are fracture healing and clinical outcome at 52 weeks after the start of treatment:

•Fracture healing will be scored by assessing union (union or non-union) and stability (stable or unstable).

o Union will be defined by evidence of bone trabeculae crossing the fracture site and absence of sclerotic borders adjacent to the fracture site, assessed using computed tomography (CT).

o Fracture stability will be assessed using upright cervical dynamic X-rays in lateral projection. A maximum of 2 mm movement at the fracture site is considered stable, over 2 mm movement at the fracture site is considered unstable [15].

•Clinical outcome; scored by calculation of the improvement compared to baseline in the Neck Disability Index (NDI) [16] score at 52 weeks after start of treatment. The NDI is a widely applied instrument to assess neck pain complaints. It was derived from the Oswestry index for back pain and the Pain Disability Index.

In the sample size calculation, the significance level was adjusted for the multiple primary outcome measures.

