### Sample size

Based on the recent literature review, the estimated possible difference in fracture union between the groups is 41% and in fracture stability this difference is 21% [12]. For both union and stability, however, a smaller difference of 20% would be clinically relevant and the study is powered to assess this difference. For the NDI, a 7.5 point difference (on a 50 point scale) is generally accepted as a minimal clinically important difference with a SD of approximately 10 in various psychometric studies [26-29]. Furthermore, it is expected that the number of patients that will be treated surgically will be twice the number of patients that are treated conservatively (2:1) [14]. Since three primary outcome hypotheses will be tested, the significance level (α) has to be divided by three. Based on the primary outcome parameters, the required sample size, assuming α = 0.05/3 = 0.0167 (two-sided) and β = 0.20 (80% power) and an expected drop out rate of 10%, is 275 for union, 198 for stability and 93 for the NDI. In conclusion, 275 patients will need to be recruited in order to give a reliable conclusion to the comparison of union, stability and clinical outcome between the surgically and conservatively treated groups.

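### The secondary NDI responder rule (improvement of 7.5 of 50 points) cannot be met by a patient who starts below 7.5, and no entry criterion excludes such patients

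*Protocol article*

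**What the plan says.** All references are to the protocol article.

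- **Primary outcome:** clinical outcome is "scored by calculation of the improvement compared to baseline in the Neck Disability Index (NDI" at 52 weeks. The primary test works on this continuous change (Univariate analysis): "T-test will be used to test for differences between groups on NDI improvement at 52 weeks".
- **Univariate analysis, secondary analysis:** the χ² "test will be used to analyse the difference in dichotomised NDI", and "NDI will be dichotomised using the criterium of the minimal clinically important change (improvement) of 7.5 points out of 50". No adjustment for baseline is attached to this test.
- **Multivariate analysis:** the plan has "regression models with dichotomised union, stability and NDI as dependent variables", with the secondary outcome parameters as independent variables and covariates. Baseline NDI appears in that section only in the list of variables for the propensity model, which predicts the treatment received.
- **Patient selection:** "All patients admitted to one of the participating centres who meet the selection criteria will be asked to participate in the study". The criteria in Table 2 concern age, fracture type, time since injury, consent and four exclusions. None is a minimum NDI.
- **Baseline assessment:** "After inclusion and prior to the start of treatment, both surgeon and patient will complete the first set of CRFs". Baseline NDI is thus measured before treatment and, by Table 2, within two weeks of injury.
- **Sample size:** "a 7.5 point difference (on a 50 point scale) is generally accepted as a minimal clinically important difference with a SD of approximately 10".

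No baseline NDI is given, either overall or by treatment group.

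**The concern.** The responder variable depends only on how far the score falls, and the room to fall is set by the starting score. A patient who goes from 6 to 0 has no remaining disability on this scale and is still a non-responder.

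Two results rest on this variable. The first is the responder rate in each group, compared by an unadjusted χ²-test. The second is the regression on dichotomised NDI, which is the only multivariate model of clinical outcome that the article describes. That model serves a stated aim of the study, to find factors that predict the success of either treatment (Discussion). If low starters cannot respond whatever happens to them, any factor that goes with a high starting score will look in part like a predictor of success.

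Treatment is chosen by surgeon and patient, and the Background names pain among the grounds for that choice. The share of low starters could therefore differ between the groups and distort their comparison as well.

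**Working it through.** **1. The plan's own figure that uses 7.5 points.** Inputs from Sample size: difference 7.5, SD 10, two-sided α = 0.05/3, power 80%, ratio 2:1, dropout 10%.

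n(conservative) = (z₁₋α/₂ + z₀.₈₀)² × SD² × (1 + 1/2) / 7.5² = (2.394 + 0.842)² × 100 × 1.5 / 56.25 ≈ 27.9, so 28. The surgical group is 56 and the total 84.

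With dropout, 84 × 1.10 = 92.4, so 93, and 84 / 0.90 = 93.3, so 94. The article states 93, so the figure reproduces. It belongs to the continuous t-test and does not depend on the responder rule.

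**2. The bound.** Improvement = baseline − week 52. The week-52 score cannot be below 0, so improvement ≤ baseline. If baseline < 7.5, improvement < 7.5 with certainty. The constraint also bites just above the cut: a patient who starts at 8 must reach 0.5 or less.

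**3. How many patients this could concern.** The baseline mean is an assumption. So is SD 10 as the spread of baseline scores, because Sample size does not give it as a baseline SD.

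The normal share is Φ((7.5 − m)/10). The version truncated to 0–50, where m is the mean before truncation, is [Φ((7.5 − m)/10) − Φ(−m/10)] / [Φ((50 − m)/10) − Φ(−m/10)]. A beta distribution on 0–50 with mean m and SD 10 serves as a check on shape.

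| Assumed mean m | Normal | Truncated normal | Beta |
|---|---|---|---|
| 15 | Φ(−0.75) = 22.7% | 17.1% | 27.7% |
| 20 | Φ(−1.25) = 10.6% | 8.5% | 11.0% |
| 25 | Φ(−1.75) = 4.0% | 3.4% | 3.6% |
| 30 | Φ(−2.25) = 1.2% | 1.1% | 1.2% |

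**4. Effect on the responder rate.** If a share f cannot respond and a proportion r of the others respond, the observed rate is r(1 − f). With an assumed r = 60% and f = 10%, the rate is 0.60 × 0.90 = 54%. Full recovery of every low starter would not change it.

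**5. Effect on the group comparison.** With the same r in both groups, the spurious difference is r × (f_C − f_S), where C is conservative and S surgical. Completers: 275 × 0.90 ≈ 248, split 165 to 83. The floor shares below are illustrations, not estimates.

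| f surgical | f conservative | Observed rates | Spurious difference | χ² rejects at 0.05 |
|---|---|---|---|---|
| 10% | 10% | 54% vs 54% | 0 points | 5% (nominal) |
| 5% | 15% | 57% vs 51% | 6 points | about 14% |
| 5% | 25% | 57% vs 45% | 12 points | about 43% |

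Equal shares give no bias between groups, however large they are.

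**The case against.** Five arguments can be made on the other side.

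- **The rule is secondary.** The primary NDI test uses continuous improvement, in which a patient going from 6 to 0 contributes 6 points. This stands: neither the primary result nor the sample size is touched.
- **Few patients may start that low.** Baseline is taken within two weeks of an acute fracture, so scores may be high. This also stands. At an assumed mean of 25 or 30 the share is only 1–4%. The article gives no baseline figure that would settle it.
- **The variable does what it says.** A change from 6 to 0 is not a change of 7.5 points, and combining change with end state would be a different endpoint. This is fair as a description of the variable. It does not help when the variable stands for clinical outcome in a model meant to find predictors of success, because part of its variation is fixed before treatment.
- **Baseline NDI is in the propensity model.** That bears on balance between treatments. Even perfect balance would only equalise the misclassification; it would not repair the responder rates or the prognostic model. The covariates stated for the outcome regressions are the secondary outcome parameters, and NDI is not among them.
- **Such detail belongs in a statistical analysis plan.** That would answer a missing rule. Here the rule is stated, and as stated it misclassifies.

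A reader might go further and infer that the rule works unevenly between the groups, to the disadvantage of conservative care, or that listing NDI in the propensity model shows that a baseline difference is expected. The documents support neither. They give no NDI by group, pain as a ground for treatment makes imbalance possible without showing it or its direction, and a propensity list names candidate confounders.

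**Conclusion.** The point holds as a defect of a secondary endpoint. By arithmetic alone, patients with baseline NDI below 7.5 cannot be responders, nothing in the selection criteria keeps them out, and they enter both the χ²-test and the NDI regression as non-responders. Responder rates are understated, and apparent predictors partly reflect a high starting score.

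The size is unknown, because it depends on a baseline distribution that the article does not give. The shares in the working run from about 1% at mean 30 to about 17–23% at mean 15 under a normal shape with SD 10, and both mean and SD are assumptions. Bias between the treatments is conditional: it is zero if the shares of low starters are equal, and the 6 and 12 points shown are illustrations. The primary NDI conclusion is unaffected. This is a cheap improvement worth making, not a threat to the main result.

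**What to change.** 1. Run the χ²-test on dichotomised NDI and the NDI responder regression in patients with baseline NDI of at least 7.5.
2. Include baseline NDI as a covariate in the responder regression, because patients just above 7.5 still have little room to improve.
3. Report the number of patients with baseline NDI below 7.5 in each treatment group.
4. Keep the all-patient version as a sensitivity analysis.

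This needs wording only and no new data. The restriction uses a score taken before treatment, so it does not select on outcome, but the responder result then applies to patients who start at 7.5 or more. The cost is the patients who leave this analysis. Of about 248 completers, the normal and truncated normal shares imply about 3 at mean 30 (248 × 0.011 to 0.012), 8–10 at mean 25 (248 × 0.034 to 0.040), and 42–56 at mean 15 (248 × 0.171 to 0.227). The loss is largest where the unrestricted rule misclassifies most.

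An alternative that also counts a low 52-week score as response should be at most a further sensitivity analysis. A patient who starts at 3 and stays at 3 would then be a responder without any improvement, so low starters would turn from certain non-responders into near-automatic responders.

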## Discussion

In this article the rationale and design of a prospective cohort study on surgical versus conservative treatment for odontoid fractures in the elderly is described. There is a lacuna in evidence-based knowledge and guidelines in treating this patient population. To the authors’ knowledge, only one prospective study on this subject has yet been published, involving 159 patients ≥65 years with type II fractures but focusing just on characteristics associated with treatment success or failure and not on describing fracture healing [14]. However, the INNOVATE Trial will specifically aim to evaluate the outcome separately for patients younger and older than 80 years. Moreover, not only fracture union, but also fracture stability will be evaluated in the INNOVATE trial, which will be correlated to clinical outcome. A combination of (relative) fracture stability and favourable clinical outcome might be a legitimate endpoint of treatment in elderly patients, although long term effects have to be investigated. The objective of this trial is to identify which treatment strategy is most favourable for elderly patients with acute type II and III odontoid fractures and to identify factors that predict the success of either one of the available treatment in individual patients. The results of this trial will yield valuable information enabling more rational decision making in the treatment of odontoid fracture in elderly patients.

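### The only healing–NDI analysis the article specifies is unadjusted for treatment or age, and neither of its two splits isolates stable non-union from union

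*Protocol article*

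**What the plan says.** The Secondary analysis bullet of the Univariate analysis section says the relation between the radiological results and NDI will be examined by "comparing the average NDI improvement for patients that acquired union/stability with those that did not". The section's tool for such a comparison is "T-tests for continuous outcomes". It mentions no stratification or adjustment by treatment or age, and no joint classification of union and stability.

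The Multivariate analysis section follows. Its regressions take union, stability and dichotomised NDI as dependent variables and the secondary outcome parameters as predictors. Union and stability are primary outcomes, so they are not among the named predictors of NDI. The propensity score, where age and baseline NDI appear, models the treatment received.

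Treatment is not randomised: "The treating surgeon and patient will make a shared decision as to whether surgical or conservative treatment will be applied".

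The Background explains why the link matters: "There is no evidence that clinical outcome correlates better to fracture union than to fracture stability". It adds that the influence of osseous versus fibrous union on outcome is likewise unknown. The Discussion promises that "not only fracture union, but also fracture stability will be evaluated in the INNOVATE trial, which will be correlated to clinical outcome", and suggests that "A combination of (relative) fracture stability and favourable clinical outcome might be a legitimate endpoint of treatment in elderly patients".

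**The concern.** There are two separate weaknesses.

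**Confounding.** The Background reports union in 66–85% of surgical and 28–44% of conservative patients, and stability in 82–97% and 53–79%. It concedes that patient selection may have distorted these figures. Healing status is therefore partly a marker of treatment. If treatment affects neck disability by any route other than healing, the pooled comparison credits or debits that effect to healing. The article itself points to such routes: surgery may worsen a frail patient's condition (Background), and extending a posterior fixation further restricts neck motion (Surgical treatment). Age is a plausible second confounder. It guides treatment choice (Background), and its influence on outcome is a stated focus.

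**Classification.** Whether outcome follows union or stability, and whether fibrous union is good enough, turns largely on how patients with a stable non-union compare with those who unite. Neither planned split makes that comparison.

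At stake is the evidence on whether union or stability should be the goal of treatment. The pooled contrast could suggest a link that is really a treatment or age effect, or mask a real one.

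**Working it through.** **The plan's own figure.** The article gives no sample size for the healing–NDI comparison. The nearest figure is 93 for the NDI treatment comparison (7.5 points, SD 10, α = 0.0167 two-sided, 80% power, 2:1). The normal approximation gives 28 + 56 = 84, and 84 × 1.10 = 92.4, so 93 is reproduced (84 / 0.90 would give 94). The SD of 10 is carried forward.

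**Inputs from the article.** 2:1 surgical to conservative; 275 recruited with 10% dropout, so 275 × 0.9 = 247.5 evaluable, about 165 surgical and 82.5 conservative; healing rates as in the Background.

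**Inputs assumed.** D, a direct effect of treatment on NDI not acting through healing: 0, 5 or 7.5 points. Healing itself is given no effect. The significance level is two-sided 0.05 where one is needed.

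**Step 1: spurious union gap.** Gap = D × [P(surgery | union) − P(surgery | non-union)]. With union 75% v 40%, which lies within the Background ranges:
- P(surgery | union) = (2/3 × 0.75) / (2/3 × 0.75 + 1/3 × 0.40) = 0.789
- P(surgery | non-union) = (2/3 × 0.25) / (2/3 × 0.25 + 1/3 × 0.60) = 0.455
- Difference = 0.335 (unrounded shares)

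| D (points) | Spurious gap (points) |
|---|---|
| 0 | 0 |
| 5 | 1.7 |
| 7.5 | 2.5 |

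The sign follows the sign of D.

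**Step 2: range over the article's rates, D = 7.5.** "Matched ends" takes both groups at the low, middle or high end of their ranges.

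| Split | Gap, matched ends | Gap, all pairings | False significance, matched ends |
|---|---|---|---|
| Union | 2.5–3.3 | 1.5–4.2 | about 52–66% |
| Stability | 2.4–3.7 | 0.3–5.0 | about 36–40% |

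Halving D to 3.75 halves the gaps and lowers false significance at matched ends to about 17–22% (union) and 13–14% (stability).

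**Step 3: how many patients the splits hide.** If every united fracture is stable, the stable non-union percentage is the stability rate minus the union rate. For conservative patients this is 66 − 36 = 30% at the midpoints, running from 53 − 44 = 9% to 79 − 28 = 51%.

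**Step 4: is a three-state comparison feasible?** At midpoint rates:
- Union: 165 × 0.755 + 82.5 × 0.36 ≈ 154
- Stable non-union: 165 × 0.14 + 82.5 × 0.30 ≈ 48
- Unstable: the remaining 45

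Unadjusted power for 7.5 points is then about 99% (union v stable non-union) and 95% (stable non-union v unstable). For 5 points it is about 86% and 68%.

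**Step 5: within the surgical group.** Unstable patients would number 165 × 0.03 ≈ 5 to 165 × 0.18 ≈ 30.

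**The case against.** A reader might infer that the planned comparison cannot answer the trial's question at all. The documents do not support that. They frame the link as a correlation, and mean NDI improvement by union and by stability describes such an association. The crude means are legitimate description. They fall short when read as showing that healing drives outcome, or that union or stability is the better target.

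A reader might also infer that the plan merges stable with unstable non-unions throughout. Only the union split does so; the stability split separates them but places stable non-unions with unions.

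A third tempting reading is that the bias is known and clinically important. It is not known. The article says data are insufficient to determine any difference in clinical outcome between treatments, so D is an assumption, and with no direct treatment or age effect there is no such bias. For D up to 7.5 points, every gap computed stays below the 7.5-point threshold.

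Finally, an article condenses, and an adjusted model may exist in a full protocol or analysis plan. It therefore cannot be said that only the crude contrast will be run. What stands is that the article specifies a method for this aim, and the multivariate section that follows does not name healing as a predictor of NDI.

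**Conclusion.** The point holds in limited form. As specified, the healing–NDI comparison is crude, pools treatments that were not randomised, and does not separate stable non-union from union.

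The confounding is possible, not demonstrated. Its illustrated size, 0 to 2.5 points at union rates of 75% v 40%, rests on an assumed direct treatment effect of 0 to 7.5 points. No age effect was quantified. Gaps of this size fall short of clinical importance but could still produce or mask a statistically significant link.

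The classification weakness needs no assumption about D. Only the size of the hidden group does: 9–51% of conservative patients is a wide range, and it supposes that all united fractures are stable.

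This is a secondary analysis. The three primary comparisons and the sample size of 275 are unaffected.

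**What to change.** Keep the crude means as description. Add a regression of 52-week NDI on healing state in three levels (union; non-union but stable; unstable), adjusted for treatment group, age and baseline NDI. Name two contrasts in advance: union v stable non-union, and stable non-union v unstable. State how a fracture read as united on CT but unstable on dynamic X-ray will be classed. Show treatment-specific results descriptively only, because so few unstable surgical patients are expected.

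The change is to analysis wording. Table 3 already schedules CT, dynamic X-ray and NDI at 52 weeks. Adjustment will cost some precision relative to the unadjusted power shown above. Residual confounding, for example by frailty or injury severity, may remain, so the result should still be reported as an adjusted association.
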